## Abstract

**Background:**

Tobacco is consumed by two-thirds of individuals with severe mental illness (SMI). Despite a high tobacco-related disease burden, there is a lack of evidence-based cessation interventions for individuals with SMI living in low- and middle-income countries. This study aims to evaluate the feasibility and acceptability of a culturally adapted behavioural intervention for tobacco cessation (SCIMITAR-SA) delivered in mental health services in Bangladesh, India, and Pakistan.

**Methods:**

A two-arm, parallel-group, individually randomised, multi-country feasibility trial will be conducted across six mental health facilities in urban centres. All trial participants will receive Very Brief Advice (VBA) and an educational leaflet from their clinical team. Additionally, those in the intervention arm will receive up to seven structured behavioural support sessions. Salivary cotinine and anabasine will be used to biochemically verify abstinence at seven months post-randomisation. Quantitative outcomes will assess feasibility of conducting a definitive trial, including recruitment and retention rates, session attendance, completeness of baseline assessments and outcome measures at four and seven months and use of health resources. An embedded process evaluation will explore the feasibility and acceptability of trial processes, and of the delivery and receipt of the VBA and SCIMITAR-SA interventions. Economic outcomes will assess the feasibility of collecting cost and resource-use data to inform a future definitive trial.

**Discussion:**

The SCIMITAR-SA trial will provide essential evidence on the feasibility of delivering culturally adapted cessation support for people with SMI in South Asia and inform scalable integration into routine psychiatric care across low- and middle-income settings.

**Registration:**

ISRCTN registry (ISRCTN91038721)

## Introduction

1

Mental disorders are a major contributor to the global disease burden, ranking among the top ten causes of health loss worldwide [1]. Individuals with Severe Mental Illness (SMI) (Schizophrenia, Schizoaffective disorder, Psychosis, Bipolar illness and Severe Depression with/without psychosis) represent one of the most vulnerable population groups [2]. They face pronounced health disparities, physical multimorbidity [3], higher mortality, shorter life expectancy, driven by both biological and behavioural factors such as smoking, poor diet, drug use, and inactivity [[3], [4], [5]]. Tobacco consumption is a major modifiable cause of morbidity and mortality, resulting in more than seven million deaths annually and contributing to prolonged disability and suffering from tobacco-related conditions [6].

Around two in three individuals with SMI are current smokers [7] and reducing tobacco use in this group is recognised as an effective strategy to narrow the life expectancy gap [8]. South Asian LMICs, particularly Bangladesh, India, and Pakistan bear the highest burden of tobacco-related disease, encompassing both smoking and smokeless tobacco (SLT) [[9], [10], [11]]. While data from the region are limited, smoking prevalence as high as 50% among individuals with SMI [12], and widespread use of SLT in the general population [13] is reported. Despite population-level declines in tobacco use over the past four decades, little reduction has occurred among individuals with SMI [14,15]. A multi-country survey in Bangladesh, India, and Pakistan reported higher tobacco use among people with SMI, especially men, yet only 38.4% had received advice to quit [16].

Although individuals with SMI are often motivated to improve their physical health, including quitting tobacco, they require tailored cessation support due to complex treatment regimens, higher dependence, and the need for psychotropic medication adjustment, differing literacy levels, cognitive difficulties, medication affecting self-efficacy and motivation [[17], [18], [19]].

Evidence from high-income countries, notably the UK SCIMITAR trial, has demonstrated that SMI-specific interventions significantly increase quit rates, improve quality of life, and are cost-effective [17].

However, these findings cannot be directly translated to LMICs, where tobacco consumption varies and includes non-cigarette products (bidi and hookah) and SLT products, and where health system capacities, cultural norms, and resource contexts differ substantially [[18], [19], [20], [21]]. No large-scale, contextually adapted cessation trials for individuals with SMI exist in these settings, representing a critical evidence gap [22,23]. Conducting a feasibility trial is therefore essential to assess intervention acceptability, relevance, and operational practicality of its delivery, and to enable refinement of our approach to its integration within the diverse contexts before evaluating effectiveness in a definitive trial [[24], [25], [26]]. The Smoking Cessation Intervention for Severe Mental Ill Health–South Asia (SCIMITAR-SA) has been adapted from the UK National Centre for Smoking Cessation and Training (NCSCT) Standard Treatment Programme [27], drawing on evidence from two South Asian cessation trials, IMPACT4S (smoking cessation support for people with SMI) [28] and ASTRA (SLT users) [29], and expanded to support dual tobacco users. Adaptation involved community engagement and involvement workshops, pre-testing with individuals with SMI and intervention delivery staff, and stakeholder consultations across Bangladesh, India, and Pakistan to guide context-specific modifications. SCIMITAR-SA follows a patient-centred approach, tailoring support and promoting autonomy in culturally aligned cessation choices, and aims to address this gap through a feasibility randomised controlled trial across Bangladesh, India, and Pakistan to lay a robust groundwork for a future definitive trial and strengthen broader efforts toward tobacco control in this population.

### Aim of the study

1.1

We aim to conduct a feasibility randomised controlled trial of SCIMITAR-SA to inform the design and implementation of a future definitive trial for tobacco cessation in mental health settings of three South Asian countries.

### Research questions for the study

1.2

1.Is it feasible to identify individuals with SMI who use tobacco, recruit them to a trial of tobacco cessation conducted in mental health facilities and retain them for up to seven months?2.Is it feasible to collect data for the primary (seven months biochemically-verified continuous abstinence) and secondary outcomes of a potential full scale trial and for the economic evaluation?3.Is it feasible to deliver SCIMITAR-SA intervention in mental health facilities?4.Is SCIMITAR-SA intervention acceptable to participants, and feasible to deliver by tobacco dependence advisors and mental health facility staff in its current form, or does it need further adaptation and refinement?

## Methods

2

The feasibility trial protocol is prospectively registered (ISRCTN91038721) and adheres to SPIRIT checklist and CONSORT guidelines [30].

### Study design

2.1

A two arm, parallel group, individually randomised, multi-country, multicentre, external pilot trial of the SCIMITAR-SA intervention will be conducted, with an embedded qualitative process evaluation and a preliminary economic evaluation.

### Study settings

2.2

The feasibility trial will be conducted across six mental health facilities in three South Asian countries: two in Bangladesh (National Institute of Mental Health, Dhaka; Thengamara Mohila Sabuj Sangha (TMSS) Medical College, Bogura), one in India (National Institute of Mental Health and Neuro Sciences (NIMHANS), Bengaluru), and three in Pakistan (Civil Hospital,Karachi, Karwan-e-Hayat, Karachi, and Institute of Psychiatry, Rawalpindi Medical University, Rawalpindi). Sites were selected based on research infrastructure, availability of trained mental health staff, managerial engagement, and sufficient numbers of individuals with SMI.

### Study participants and eligibility criteria

2.3

Adults (≥18 years) with a confirmed diagnosis of SMI, (schizophrenia, schizoaffective disorder, bipolar affective disorder, psychosis, or severe depression with/without psychosis) and who are current users of smoked and/or smokeless tobacco and are willing to quit all forms of tobacco use, will be recruited. Participants will be identified from outpatient departments of the six participating mental health facilities. Eligible participants must be clinically stable, as assessed by the treating psychiatrist (no electroconvulsive therapy or neurostimulation in the preceding three months and <25% change in medication dosage), reside within the facility's catchment area, and provide informed consent. Inclusion requires self-reported daily or near-daily tobacco use (smoked and/or smokeless) for at least six months and ≥25 days in the past month [28], willingness to quit all forms of tobacco within 30 days, and ability to attend up to seven face-to-face counselling sessions. Only one participant per household will be enrolled to avoid risk of contamination. Exclusion criteria are minimal and include self-reported use of e-cigarettes, heated tobacco products, or oral nicotine pouches in the past 30 days and/or in combination with either smoking and/or smokeless forms of tobacco; comorbid drug or alcohol use; personality, eating, neurodevelopmental or post-traumatic stress disorders; receipt of pharmacological and/or behavioural cessation support (beyond brief advice) within the previous 30 days; and dual users who are willing to quit only one form of tobacco.

### Details of interventions

2.4

The details of each are given below. All participants with SMI will receive usual care, including Very Brief Advice (VBA) and a self-help educational leaflet. Participants allocated to the intervention arm will, in addition, receive the SCIMITAR-SA intervention.

### Very Brief Advice

2.5

VBA, developed by the UK National Centre for Smoking Cessation and Training, is a three-step evidence-based approach comprising Ask (about their tobacco use), Advise (about quitting), and Act (to prompt quit attempts through available cessation resources) [31,32]. VBA has been adapted from the ASTRA smokeless tobacco cessation trial [33]. It will include a brief conversation on tobacco use status (smoked and/or smokeless), advice to quit and providing a self-help educational leaflet [34]. VBA will be delivered by health professionals during outpatient visits in interactions lasting up to 1 min. Staff involved in SMI patient care will receive orientation on VBA delivery. As a low-intensity intervention, VBA satisfies ethical duty-of-care requirements while minimising contamination of the active intervention arm.

### SCIMITAR-SA intervention

2.6

SCIMITAR-SA intervention consists of up to seven individual counselling sessions (20–30 min each) delivered over approximately six to seven weeks by trained Tobacco Dependence Advisors (TDAs) experienced in caring for mental health patients (specialist or non-specialist) who receive specific SCIMITAR-SA training and supervision. The intervention will allow for two pre-quit sessions, a quit day session (corresponding with 30 days since enrollment) and weekly follow up to the 4-week post-quit point. In line with the findings of SCIMITAR-UK [35], the sessions may be adapted into shorter, more frequent contacts, with duration extending beyond 6-7 weeks as needed. A model of trainer-of-trainers (ToT) will supervise and support TDAs, with both groups receiving comprehensive training and follow-up discussion from behaviour change experts.

Sessions will be delivered face-to-face up to the quit day, with the option of remote delivery (phone or WhatsApp) if in-person meetings are not feasible. The intervention adopts a participant-centred approach, helping participants articulate reasons for quitting, identify triggers, and develop coping strategies. The TDAs will provide tailored information, reinforce progress, and review challenges throughout the quit journey. Caregivers may assist with logistics but will not participate in counselling sessions. Participants will receive reimbursement for their travel and time for research purposes (BDT 1000/INR 500/PKR 1500 per visit).

SCIMITAR-SA is a behavioural programme; cessation aids such as nicotine replacement therapy (NRT) are not provided but may be used if available through usual care. When participants choose to use NRT, TDAs will advise on appropriate type, dosage (quantity and strength), and potential side effects, with details recorded in case report forms at follow-up assessments (see Fig. 1).

### Details of the intervention materials

2.7

The materials that will be used for SCIMITAR-SA trial are described in Fig. 2 below:

**Fig. 1 fig1:**
[figure not shown]
Trial flow diagram.

**Fig. 2 fig2:**
[figure not shown]
Intervention materials used in SCIMITAR-SA feasibility trial.

### Identification and screening of trial participants

2.8

At each participating outpatient facility, mental-health professionals (psychiatrists, psychologists, or trainees) will identify tobacco-using individuals with a confirmed SMI diagnosis and provide a VBA + leaflet. Eligible patients will then be referred to Research Assistants (RAs) for screening. Before screening, patients will be asked for permission to be assessed for eligibility. The RA will administer a screening form to determine eligibility. Each trial site will maintain a daily screening log documenting the number of individuals assessed, their eligibility status, and reasons for ineligibility where applicable.

### Recruitment of participants for the trial

2.9

Eligible individuals will receive a translated Participant Information Sheet (Bangla, Urdu, Kannada, or Hindi) describing the study purpose, procedures, risks, benefits, confidentiality, and voluntary nature of participation. For participants unable to read or write, the information will be read aloud in the presence of a caregiver or impartial witness. Written informed consent will be obtained before any baseline assessment. Consenting participants will sign or provide a thumb impression, countersigned by a witness when required by local ethics committees. Copies of the signed consent form and information sheet will be provided to participants, with originals securely stored at the trial site. Participants may take up to one week to decide; the RA will maintain contact during this period.

Once consented, baseline data will be collected and participants randomised. Those allocated to the intervention arm will be scheduled for counselling sessions by the TDA. Participants preferring to delay consent will be logged for follow-up, and reasons for declining participation will be recorded where possible. Each screened individual will be assigned a unique study ID. Non-identifiable data (age, sex, diagnosis, tobacco-use status, eligibility outcome, and screening duration) will be entered into the (REDCap) [36] database. Identifiable data for consented participants will be stored separately in site-based logs.

Participants may withdraw consent and leave the trial at any time without giving a reason. Written contact details for withdrawal will be provided, and participants may inform any member of the research team if they wish to withdraw. No further data will be collected after withdrawal. Data collected up to that point will be retained for analysis; if data removal is requested, all personally identifiable data will be deleted while anonymised data will be retained and analysed in accordance with GDPR research exemptions.

## Randomisation and trial arm allocation

3

Participants will be randomly allocated to the intervention or control arm using consecutively numbered, sealed opaque envelopes. The randomisation schedule will be generated by a statistician at the York Trials Unit (YTU) using Stata (version 19) [37] with stratified block randomisation by site and tobacco-use type (smoked only, smokeless only, or dual users), employing variable block sizes of two and four. Each allocation will be printed on a card, sealed in an envelope, and labelled sequentially according to the schedule. Envelopes will be securely stored at each site and accessed only by authorised staff. Following baseline data collection, the RA will contact a trial coordinator at the central research office, who will open the next envelope, record the allocation, and inform the RA. The RA will document the allocation in the baseline e-CRF and notify participants. The coordinator will inform the TDA of intervention-arm participants to schedule intervention sessions.

Web-based or REDCap randomisation will not be used due to unreliable internet connectivity across participating outpatient facilities, which could compromise real-time allocation during clinic workflows. Sealed opaque envelopes will therefore be used as a pragmatic and robust approach suitable for multi-country implementation in these settings. Envelope integrity will be monitored through central oversight, sequential numbering, secure storage, and regular cross-checking of allocation logs against the master randomisation schedule.

### Blinding

3.1

Blinding of participants, mental health professionals, and research staff is not feasible. However, allocation concealment will be maintained until completion of baseline assessments. To ensure objectivity in outcome assessment, tobacco cessation status will be biochemically verified using saliva cotinine and anabasine testing. Cotinine serves as a biomarker of nicotine exposure, while anabasine differentiates tobacco use from nicotine replacement therapy.

## Baseline and follow-up data collection procedures

4

After recruitment, data will be collected from participants, with or without the support of caregivers, at baseline (after informed consent and prior to randomisation) and at four and seven months post-randomisation. The trained RAs will administer all instruments in person using REDCap [36] on electronic tablets. Participants in the intervention arm will have a 30-day grace period to set their first quit date, and all follow-up assessments will take place at four and seven months after randomisation.

The information collected at each follow-up, is summarised in Table 1.

**Table 1 tbl1:** Baseline and follow-up data collection procedures.

	Measurement/data collection	Baseline	4 month follow-up	7 month follow-up
1	Socio-demographic and household information	X		
2	History of tobacco use and attempts to quit	X		
3	Quick SCID (module A and B only)	X		
4	Brief Psychiatric Rating Scale (BPRS)	X		X
5	Self-reported abstinence from tobacco products (past 7-days and since quit date)		X	X
6	Salivary cotinine and anabasine (for biochemical verification)			X
7	Nicotine dependence and urge to use tobacco	X	X	X
8	Quitting intentions, motivations and behaviour	X		
9	Health-related quality of life	X	X	X
10	Mental and physical health	X	X	X
11	Health service utilisation	X	X	X
12	Physical measurements – height and weight, waist circumference Vital signs (Blood pressure, heart rate)	X	X	X
13	Researcher meetings to discuss trial processes	X	X	X
14	Interviews with mental health staff and managers to discuss trial processes and SCIMITAR-SA implementation		X	
15	Focus group discussions with TDAs to discuss SCIMITAR-SA delivery, implementation and administration		x	
16	Interviews with dual users to gather feedback on trial processes and the SCIMITAR-SA intervention		X	
17	Participant session records held by TDAs		X	

**At baseline**, data will be obtained on socio-demographic characteristics (age, gender, education, occupation, marital status, and household assets to determine socioeconomic status using items from the ASTRA trial) [38] and diagnosis of SMI confirmed through the Quick SCID [39]. The psychiatric symptom severity will be assessed at baseline and seven months using the Brief Psychiatric Rating Scale (BPRS) [40]. The history of tobacco use (age at initiation, type, frequency, duration, and prior quit attempts) will be collected using items adapted from the ASTRA [38], Quit4TB and IMPACT-4S [28] trials. Nicotine dependence will be measured using the adapted Heaviness of Smoking Index from ASTRA trial [38], withdrawal symptoms using the Mood and Physical Symptoms Scale (MPSS) [41] and motivation to quit through the Motivation to Quit (MTQ) questionnaire [42]. The EQ-5D-5L [43] will assess health-related quality of life(HRQoL), while the PHQ-9 [44], GAD-7 [45], and SF-12 [46] will measure depressive and anxiety symptoms and physical and mental health status, respectively.

**At four months follow-up**, data collection will focus on tobacco-use outcomes, nicotine dependence, withdrawal symptoms, health-related quality of life, mental and physical health, health-service utilisation, and anthropometric measures. Specifically, tobacco-use status since the quit date and in the previous week will be assessed using items from the ASTRA trial [38], including any use of nicotine products (such as e-cigarettes or nicotine oral pouches). Nicotine dependence will be measured using the adapted Heaviness of Smoking Index from ASTRA trial [38], withdrawal symptoms using the Mood and Physical Symptoms Scale (MPSS) [41]. The EQ-5D-5L [43] will assess health-related quality of life(HRQoL), while the PHQ-9 [44], GAD-7 [45], and SF-12 [46] will measure depressive and anxiety symptoms and physical and mental health status, respectively. Health-service use and out-of-pocket expenditures will be captured using a questionnaire adapted from previous trials (ASTRA [38], POTENTIAL [47], and RESPIRE [48]) and height and weight will be recorded to calculate BMI following WHO protocols [49].

**At seven months follow up,** all measures from the four-month assessment and BPRS will be repeated, and an additional salivary sample will be collected to biochemically verify abstinence. We will operationalise the biochemically verified continuous abstinence from all tobacco products using the global Russell Standard of sustained and verified quitting [50]. For those who report using tobacco products on no more than 5 occasions during the cessation period (duration between the target quit date (for intervention group) or 30 days post-randomisation (for the control group) and the seven month follow up time point) at the seven-month follow-up, biochemical verification will be carried out through salivary cotinine and Anabasine testing through LC-MS (ACM Global Laboratories, UK for Bangladesh and Pakistan & Laboratory of the Department of Clinical Psychopharmacology and Neurotoxicology for India). Cotinine level <15 ng/ml will be used to identify biochemically verified abstinence), whereas those who self-report continuous abstinence but have cotinine levels above the threshold will be identified as tobacco users. Biochemically verified tobacco abstinence at seven months is included as an exploratory outcome to assess the feasibility of collecting cessation outcome data, including biochemical verification, and to inform outcome selection, measurement procedures, and sample size estimation for a future definitive trial.

Follow-up assessments at four and seven months post-randomisation will be considered on time if completed within a one-week window before or after the scheduled date. RAs will begin contacting participants one week prior to, and for up to three weeks after, each due date, making up to three phone calls per week at varying times and days to schedule the assessment. Instances of delayed follow-up will be documented and reviewed after the feasibility phase to refine procedures for the main trial. If the four-month data are missed, efforts will still be made to obtain information at the seven-month follow-up.

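### The abstinence window opens at the target quit date in the intervention arm but at day 30 in the control arm, so the same tobacco use can be scored differently by arm

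*Protocol article*

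**What the plan says.** The outcome definition is in section 4 (Baseline and follow-up data collection procedures), under the seven-month follow-up. Biochemical verification is carried out for those who report "using tobacco products on no more than 5 occasions during the cessation period". That period starts at "the target quit date (for intervention group) or 30 days post-randomisation (for the control group" and ends at the seven-month follow-up. The laboratory criterion is common to both arms: "Cotinine level <15 ng/ml will be used to identify biochemically verified abstinence".

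The end of the window is also common, since "all follow-up assessments will take place at four and seven months after randomisation".

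The quit date itself is described in two ways:

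- Section 4: "Participants in the intervention arm will have a 30-day grace period to set their first quit date".
- Section 2.6 (SCIMITAR-SA intervention): two pre-quit sessions, then "a quit day session (corresponding with 30 days since enrollment"), then weekly contact to four weeks after quitting. Sessions may be made shorter and more frequent, "with duration extending beyond 6-7 weeks as needed".

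Table 1 lists the self-report item for the four- and seven-month visits as "Self-reported abstinence from tobacco products (past 7-days and since quit date"), without distinguishing the arms.

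On the status of the outcome, section 4 calls verified abstinence at seven months exploratory and says it will inform outcome selection, measurement procedures and sample size for a definitive trial. Section 1.2 names it as the primary outcome of a potential full-scale trial. Section 5.2 plans no formal statistical comparison.

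**The concern.** The rule that classifies a participant as abstinent should not depend on allocation. Here it does. The allowance of five occasions and the end date are fixed, but the starting point is a personal target date in one arm and a calendar date in the other. Any use between an early quit date and day 30 counts against an intervention participant and is ignored for a control participant.

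Two things are at stake. First, the same window decides who is sent for cotinine and anabasine testing, so the group assayed is selected by a different rule in each arm. Completeness of self-reported and verified abstinence is a feasibility outcome (section 5), and completeness of the primary outcome data is a progression criterion (section 5.11). Second, the definition and the rates by arm are meant to carry forward into the definitive trial, where an allocation-dependent rule would sit inside the primary comparison.

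**Working it through.** The article states no length for the cessation period, so there is no figure of its own to reproduce. No stated sample-size figure depends on this point.

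**Inputs**

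- End of window: seven months after randomisation, both arms (section 4). 7 × 30.44 = 213 days.
- Start of window, control: day 30 after randomisation (section 4).
- Start of window, intervention: target quit date, day *q* (section 4).
- Allowance: five occasions, not scaled to window length (section 4).
- Enrolment and randomisation are treated as the same day (assumption).

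**Where *q* may fall.** Section 2.6 has two pre-quit sessions, one quit-day session and four weekly follow-ups: 2 + 1 + 4 = 7 sessions over about six to seven weeks. The last session is four weeks after quit day, so quit day is about 6 − 4 = 2 to 7 − 4 = 3 weeks after the first session, that is, 14 to 21 days. If the first session is held at about the time of randomisation (assumption), *q* is about 14 to 21. For quit day to fall on day 30, the first session would have to be 30 − 21 = 9 to 30 − 14 = 16 days after enrolment. Day 30 is therefore compatible with the schedule but not guaranteed by it.

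**Window length = 213 − start day**

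| Arm and quit date | Window (days) | Ratio to control |
|---|---|---|
| Control | 213 − 30 = 183 | 1.00 |
| Intervention, *q* = 30 | 213 − 30 = 183 | 1.00 |
| Intervention, *q* = 21 | 213 − 21 = 192 | 192/183 = 1.05 |
| Intervention, *q* = 14 | 213 − 14 = 199 | 199/183 = 1.09 |

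**Classification, which matters more than length**

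- Person A uses tobacco six times between days 14 and 29 and never afterwards. Control: 0 occasions counted, so eligible for verification. Intervention with *q* = 14: 6 occasions counted, so a failure, and outside the group to be assayed.
- Person B uses it three times between days 14 and 29 and three times after day 30. Control: 3 counted, eligible. Intervention with *q* = 14: 3 + 3 = 6 counted, failure.
- Person C uses it twice between days 14 and 29 and never afterwards. Control: 0 counted. Intervention: 2 counted. Both eligible.

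A slip before day 30 changes the result only when it takes the total above five.

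**Illustrative size.** Suppose behaviour is identical in both arms and a true proportion *p* would be classed as abstinent with a day-30 start. Let *f* be the share of these who exceed the limit once use between quit date and day 30 is counted. The intervention arm is then scored *p*(1 − *f*). With *p* = 10% (assumption):

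- *f* = 0: 10.0%, no artefact
- *f* = 10%: 10 × 0.90 = 9.0%, −1.0 point
- *f* = 25%: 10 × 0.75 = 7.5%, −2.5 points
- *f* = 50%: 10 × 0.50 = 5.0%, −5.0 points

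The documents give neither *p* nor *f*, so this is a range and not an estimate.

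**The case against.** The strongest defence is that the protocol already aligns the arms. Section 2.6 puts the quit-day session at 30 days, and section 2.3 requires every participant, controls included, to be willing to quit within 30 days. On that reading day 30 is simply the control counterpart of the quit day, and both windows last 183 days. This stands as a nominal intention. It does not override the definition in section 4, which uses each intervention participant's own target date and allows it to be set within a grace period.

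The second defence is that nothing in this trial turns on the quit rate: the outcome is exploratory, there is no formal comparison, and the progression criteria use recruitment, retention and completeness. This also stands and limits the severity. It does not remove the effect on who is assayed. Whether that moves the completeness percentage depends on how participants who fail on self-report are counted, which the article does not say.

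A reader might infer more than the text supports:

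- *That the arms are judged on different outcomes.* The lapse limit, cotinine threshold and end point are shared. Only the start date can differ.
- *That the intervention window is up to 16% longer* (213/183 = 1.16). This needs a quit date on the day of randomisation, which two prior sessions make implausible.
- *That late or reset dates shorten the window and favour the intervention.* The word first in the grace-period sentence and the option to extend the sessions invite this, but no text says that the anchor moves. The extension concerns how long sessions run.
- *That controls have no start date because Table 1 asks about use since the quit date.* The text of section 4 gives them day 30, and the table is shorthand. How a participant who never sets a date is scored may be settled in the full protocol or analysis plan.

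**Conclusion.** The point holds as an allocation-dependent start to the abstinence window, of moderate severity. The windows are identical only if every intervention quit date falls on day 30. With a quit date on day 14 (assuming roughly weekly pre-quit sessions starting at about randomisation) the intervention window is about 199 days against 183, about 9% longer; on day 21 it is about 5% longer. For such early dates the rule is stricter on the intervention arm. The number of participants misclassified is unknown: it is zero if nobody crosses the five-occasion limit through use before day 30, and the 1 to 5 point range above rests wholly on assumed values. The effect on this trial's conclusions is small. The reason to act is that the rule selects who is biochemically verified, and that the definition and the rates are intended to shape the definitive trial's primary outcome and sample size.

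**What to change.** - Define the cessation period in both arms as day 30 after randomisation to the seven-month assessment. Day 30 is already the control-arm anchor. This changes how the outcome is measured and says nothing about when a participant should quit.
- Word the self-report items on sustained abstinence at four and seven months from that same date in both arms, and apply the five-occasion screen for assay to that window.
- Report abstinence since the actual quit date in the intervention arm as a descriptive extra.
- Reconcile how section 2.6, the grace-period sentence and the outcome definition in section 4 describe the quit date.

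The cost is a wording amendment to the protocol and case report form, with no extra visits or samples. Under section 6.1 the amendment must go to the sponsor's governance committee for classification: a minor one takes effect on notification, while a major one needs prior approval from the national ethics committees. It is best made before follow-up data are collected, because use counted from one date cannot reliably be recounted from another months later.
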